## Discussion

It has been indicated that plaque anatomy and composition identified by VH-IVUS is a predictor of long-term clinical outcomes in patients undergoing PCI. However, there have been few studies investigating the relationship between plaque composition of SVG by VH-IVUS and clinical outcome in SVGD patients undergoing PCI. PCI is a widely performed surgical procedure for SVGD patients. Considering the higher risk in conducting PCI among SVGD patients, it is necessary to explore the cardiovascular factors predicting the clinical outcome of PCI, which can be used for risk stratification and intervention guidance. In this prospective cohort study, we will identify atherosclerotic plaque components and characteristics in SVGD patients undergoing PCI and predict the long-term clinical outcomes identified with VH-IVUS.

Multiple novel intravascular imaging technologies have been developed to help identify high risk plaque characteristics in predicting cardiovascular adverse events [22, 29, 30]. Young Joon Hong et al. investigated the relationship between intravascular IVUS findings and the no-reflow phenomenon after PCI for SVGD [22]. But IVUS has limited value for identifying specific plaque components [31]. Computed tomography (CT) is routinely used for coronary angiography and can identify high risk features of plaques. Daniel R. Obaid et al. found that plaque components and classifications based on CT could not reliably classify plaques and identify TCFA [30]. With the highest spatial resolution, optical coherence tomography (OCT) has emerged as an important imaging modality for intracoronary evaluation [32]. The direct comparison between VH-IVUS and OCT by Brown et al. found that both VH-IVUS and OCT could identify advanced coronary plaques and that combined VH-IVUS/OCT was better than either alone [33]. However, OCT has a low signal penetration through lipid or necrotic core, and cannot adequately acquire images of the whole vessels with large lumen diameter or large necrotic core [29, 34]. This presents a problem for imaging of large vessels including vein grafts. The presence of macrophages, foam cells, microcalcifications, or hemosiderin, often co-existent with the necrotic core, could be adverse to accurate OCT assessment of lipidic plaque [29, 34]. VH-IVUS, which has become clinically available, can assess both plaque morphology and tissue characteristics using spectral and amplitude analysis of backscattered radiofrequency ultrasound signal. With different plaque components exhibiting a defined spectrum, VH-IVUS can classify atherosclerotic plaque into four types: FT, FF, NC, and DC [35, 36]. The radiofrequency signal is mathematically transformed into a color-coded representation, including lipid, fibrous tissue, calcification, and necrotic core [37]. Thus, VH-IVUS can identify atherosclerotic plaques exactly like histopathology.

Some meta-analysis studies have found that the relationship between absolute volume of NC components on VH-IVUS imaging and distal embolization after PCI in acute coronary syndrome (ACS) patients [35, 38]. Previous studies have demonstrated that TCFA, plaque burden, and minimum luminal area are associated with MACEs among ACS patients undergoing PCI [25, 26]. The VIVA (VH-IVUS in Vulnerable Atherosclerosis) Study showed that VH-IVUS TCFA was associated with nonrestenotic and total MACEs on individual plaque or whole patient analysis [26]. It was reported by the Providing Regional Observations to Study Predictors of Events in the Coronary Tree (PROSPECT) study that plaque burden > 70%, minimum luminal area < 4 mm^2^, and VH-IVUS TCFA were the independent predictors of nonculprit lesion–related events. However, there are limited studies investigating the associations of degenerative lesions or plaque components of SVGD with clinical outcomes using VH-IVUS. Man-Hong Jim et al. sought to report the VH-IVUS findings in degenerative aortocoronary SVG lesions and correlate plaque compositions with clinical characteristics [39]. Lesions with a plaque burden ≥70% was found to be positively correlated with FF tissue, but negatively correlated with DC [39]. However, it is a cross-sectional study, the temporary relationship between VH-IVUS findings and clinical characteristics cannot be determined. As far as the authors know, there is currently no study exploring the relationship between VH-IVUS defined atherosclerotic plaque components and clinical outcomes in SVGD patients undergoing PCI.

The current study is subject to several limitations. This is an observational cohort study, confounding effects cannot be ruled out entirely. However, the multivariate Cox proportional regression model will be used to determine the independent effects of VH-IVUS findings on long-term clinical outcomes after adjusting for the impact of baseline characteristics. Second, participants with SVGD who are enrolled in a single center (Cardiovascular Institute, Tianjin Chest Hospital) may not represent the population in China. However, we speculate that the relationship between VH-IVUS findings and clinical outcomes should persist in other SVGD patients undergoing PCI, but with varying magnitudes of association. Third, although VH-IVUS is a widely used method in clinical setting, VH-IVUS has some technological limitations. VH-IVUS TCFA is not equivalent to histopathologic definitions and VH-IVUS tend to over-estimate TCFA compared with histology.

## Conclusion

The proposed prospective cohort study aims to investigate whether plaque characteristics and components of culprit SVG lesion assessed by VH-IVUS could predict subsequent clinical outcome after PCI among SVGD patients. Once our hypothesis is confirmed, an innovative prediction tool of clinical outcomes can be created, which may lead to the development of new methods of risk stratification and intervention guidance.

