**Discussion:**

Once the predictive values of plaque components and characteristics by VH-IVUS on subsequent clinical outcomes are determined among SVGD patients undergoing PCI, an innovative prediction tool of clinical outcomes for SVGD patients undergoing PCI will be created, which may lead to the development of new methods of risk stratification and intervention guidance.

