### Sample size

We expect CAS of plaque and media 2.9 ± 1.7 mm^2^ among patients with MACEs and 1.9 ± 1.5 mm^2^ among patients without MACEs. It is estimated that the incidence of MACEs is 20% in 3 years after PCI for SVGD. Assuming a 20% drop-out rate, a total of 175 participants are required to provide 80% power, with a two-sided type I error of 0.05.

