### Statistical analysis

Analyses will be made using SAS statistical software (version 9.3) by researchers at the Peking University Clinical Research Institute. Continuous variables will be expressed as mean ± standard deviation or median ± interquartile range (IQR), and t-test or Wilcoxon rank sum test will be used to compare the difference between groups. For categorical variables, the chi-square test/ Fisher’s exact test will be performed. Time-to-event data (MACEs in 3 year after PCI) will be presented as Kaplan-Meier estimates and the primary outcome analysis will be carried out using univariate and multivariate Cox proportional hazards regression models. The ideal cut-off of quantitative indexes of VH-IVUS and the diagnostic accuracy will be determined by the receiver-operating characteristic curve (ROC). A *p*-value < 0.05 will be considered statistically significant in all analyses.

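### The stated accuracy analysis covers VH-IVUS indexes alone, so the plan tests independent association but does not measure what VH-IVUS adds to clinical prediction, although it goes on to a prediction tool

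*Protocol article*

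**What the plan says.** The hypothesis in the Background is one of association between plaque characteristics and long-term outcome. The Statistical analysis section makes univariate and multivariate Cox regression the primary outcome analysis, and the limitations paragraph of the Discussion explains that the multivariate model is there to isolate the effect of VH-IVUS findings from baseline characteristics.

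Accuracy is dealt with in one sentence of the Statistical analysis section: "The ideal cut-off of quantitative indexes of VH-IVUS and the diagnostic accuracy will be determined by the receiver-operating characteristic curve (ROC"). The significance rule is general: a p-value below "0.05 will be considered statistically significant in all analyses". The article names no clinical-only model as a benchmark and no comparison of discrimination with and without VH-IVUS.

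The Discussion part of the Abstract says that, once predictive values are determined, "an innovative prediction tool of clinical outcomes for SVGD patients undergoing PCI will be created". The Conclusion is softer but makes the same step: "Once our hypothesis is confirmed, an innovative prediction tool of clinical outcomes can be created, which may lead to the development of new methods".

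The Sample size section gives the effect that the study is built on: "We expect CAS of plaque and media 2.9 ± 1.7 mm^2^ among patients with MACEs and 1.9 ± 1.5 mm^2^ among patients without MACEs".

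**The concern.** The article moves from a confirmed association to a tool for risk stratification and intervention guidance. Two results would support that step: an adjusted hazard ratio and a stand-alone AUC. The hazard ratio shows whether VH-IVUS carries information beyond the adjusted covariates. The AUC shows how well the index ranks patients when nothing else is known about them. Neither gives the quantity that decides whether an invasive imaging measure is worth putting in a risk tool, namely how much better patients are ranked once it is added to history, examination, laboratory results and angiography. All of these are recorded under Baseline assessment and follow-up.

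This is a separate matter from optimism in a data-derived cut-off or from overfitting. It would remain with perfectly unbiased estimates.

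**Working it through.** **Inputs from the article.** Plaque-and-media area 2.9 (SD 1.7) mm² with MACEs and 1.9 (SD 1.5) mm² without, a difference of 1.0; MACE incidence 20%; drop-out 20%; 80% power; two-sided alpha 0.05 (all from Sample size).

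**1. Reproduce the sample size.** Two means, unequal variances, 1:4 ratio, normal approximation:

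n(MACE) = (1.960 + 0.842)² × (1.7² + 1.5²/4) / 1.0² = 27.1, rounded up to 28.

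28 + 4 × 28 = 140, and 140 / (1 − 0.20) = 175. This matches the article exactly, so 28 MACE and 112 non-MACE evaluable patients is the right basis for what follows.

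**2. Stand-alone AUC at the planning values (binormal).**

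AUC = Φ(1.0 / √(1.7² + 1.5²)) = Φ(0.441) = 0.670.

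The Hanley-McNeil standard error with 28 and 112 patients is 0.061, so the 95% CI is 0.670 ± 1.96 × 0.061, about 0.55 to 0.79.

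**3. AUC at a just-significant unadjusted difference.**

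Difference = 1.96 × √(1.7²/28 + 1.5²/112) = 1.96 × 0.351 = 0.69 mm².

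AUC = Φ(0.69 / √(1.7² + 1.5²)) = 0.62.

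**4. Gain implied by a just-significant adjusted term.** The article gives no clinical-model AUC, so I assume 0.60 to 0.70. I also assume a binormal model with equal variances and a normal approximation to the Cox test.

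The clinical score has separation d = √2 × Φ⁻¹(AUC). The part of the index not explained by the clinical score has separation d(adj), tested by z = d(adj) × √(28 × 112 / 140) = 4.733 × d(adj). Just reaching z = 1.96 needs d(adj) = 0.414, so d(adj)² = 0.1715. The combined AUC is Φ(√((d² + d(adj)²) / 2)).

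| Assumed clinical AUC | d² | d² + 0.1715 | Combined AUC | Gain |
|---|---|---|---|---|
| 0.60 | 0.128 | 0.300 | 0.651 | 0.051 |
| 0.65 | 0.297 | 0.468 | 0.686 | 0.036 |
| 0.70 | 0.550 | 0.721 | 0.726 | 0.026 |

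**5. Gain when the index has exactly the planned AUC of 0.67.** Here the gain depends on the assumed within-group correlation between index and clinical score. At a clinical AUC of 0.70 it is 0.053, 0.027 and 0.013 for correlations of 0, 0.3 and 0.5. At 0.65 it is 0.071, 0.047 and 0.035. The same stand-alone AUC is therefore compatible with quite different amounts of added value.

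**6. Can the gain be tested?** A simulated DeLong test of the gain (1,000 runs per setting, 28 and 112 patients, clinical AUC 0.65 to 0.75, correlation 0 to 0.5, weights treated as known) had power of about 5% to 33%. The gain can be estimated, but not usefully tested.

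**The case against.** The strongest reply is that VH-IVUS is not judged without reference to clinical variables, because the primary analysis includes a Cox model adjusted for baseline characteristics. That stands. A significant VH-IVUS term in that model is real evidence of prognostic information beyond the covariates. For a single VH-IVUS measure, a likelihood-ratio test of nested models would largely repeat it.

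A reader might go further and infer that a confirmed hypothesis is compatible with almost no gain in prediction. The documents do not support that. A near-zero gain arises only by fixing the stand-alone AUC at 0.67 and ignoring the adjusted test. Take an assumed clinical AUC of 0.70 and correlation of 0.7. The gain is then about 0.0035, but d(adj) is 0.147 and the expected z is 4.733 × 0.147 = 0.69, so the adjusted term would reach significance only about 11% of the time. The planned model would usually not confirm the hypothesis in that setting.

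A reader might also infer that the article claims superiority over a clinical model, or sets p < 0.05 as a rule for building the tool. It does neither. The Conclusion is hedged and concerns later work; the wording in the Abstract is firmer.

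Finally, this is a condensed article and no SAP is shown, so added-value measures may be specified elsewhere, and their absence here is not in itself a fault. What remains is that the only accuracy analysis the article states does not match the use it announces for the result.

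**Conclusion.** The point holds in a limited form. The adjusted Cox model answers the association question. The stated accuracy analysis does not answer how much VH-IVUS adds to clinical prediction, and the tool statements in the Abstract and the Conclusion need that answer.

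The AUCs of 0.67 at the planning values and 0.62 at a just-significant unadjusted difference follow from the article's own figures, given normality within each group. The gain of about 0.03 to 0.05 at a just-significant adjusted term rests also on the assumed clinical AUC of 0.60 to 0.70 and on the approximations shown.

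The association analysis and the sample size are unaffected. With about 28 expected events, this is a modest improvement in reporting and not a defect in the study's main analysis.

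**What to change.** **Statistical analysis section.** Beside the stand-alone ROC, report the concordance of the Cox model with baseline clinical variables only and of the same model with the VH-IVUS measure added, in the same patients. Give the change with a bootstrap 95% CI, as an estimate and not as a formal test.

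**Abstract (Discussion) and Conclusion.** Make the prediction-tool statement depend on that added value, or limit the conclusion to independent association.

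**Cost.** A few lines of analysis code and some wording; no new data, visits or patients. The drawback is that the added-value figure will look less favourable than the stand-alone AUC and will be imprecise with about 28 events.

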## Abbreviations

ACS: Acute coronary syndrome
CABG: coronary artery bypass grafting
CAD: coronary artery disease
CAS: cross-sectional areas
CT: Computed tomography
CTFC: Corrected TIMI frame count
DC: dense calcium
EEM: external elastic membrane
FCa: fibrocalcific plaque
FF: fibrofatty
FT: fibrous tissue
IVUS: intravascular ultrasound
MACEs: major adverse cardiac events
NC: necrotic core
OCT: Optical coherence tomography
PCI: percutaneous coronary intervention
PIT: Pathologic intimal thickening
PROSPECT: Providing Regional Observations to Study Predictors of Events in the Coronary Tree
ROC: Receiver-operating characteristic curve
SVGD: saphenous vein grafts disease
SVGs: saphenous vein grafts
TCFA: Thin-cap fibroatheroma
ThCFA: Thick-cap fibroatheroma
TIMI: Thrombolysis in myocardial infarction
TLR: target lesion revascularization
TVR: target vessel revascularization
VH-IVUS: virtual histology intravascular ultrasound
